### Study subjects

The study focuses on adolescent patients with SCD and their caregivers. The patient-caregiver dyad is included. The inclusion period is expected to be 2 years.

#### Inclusion criteria

Patients are included if they fulfil the following conditions: having the SS, SC, or Sβ form of SCD; aged between 16 and 17 years; orally agreeing to participate. The caregiver is included if they fulfil the following conditions: parent or legal guardian of the patient; aged more than 18 years; having provided a signed written consent for him/herself and for the patient.

#### Non-inclusion criteria

Patients and caregivers with any of the following conditions are excluded: presence of any known and major cognitive or psychiatric disorder that could, according to the judgement of the investigator, hamper intervention or evaluation, and/or familial history of such disorder; patients considered healed after stem cell transplantation. No concomitant care, interventions, or enrolment to other trials are prohibited by participation in the DREPADO trial.

#### Withdrawal and discontinuation

Participants can withdraw voluntarily at any time during the trial. Participants who are not present at intervention and/or evaluation are contacted by telephone; after four unsuccessful calls, participants are considered dropouts.

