### Sample size and recruitment

A total of 196 (98 in each group) is required to detect at least a 15% reduction of the hospitalisation rate for complications 2 years after the transfer in the intervention group compared to the control group. This reduction assumes a hospitalisation rate of 3.5 per patient per year [7] with 80% power and the use of a two-sided test at a significance level of 5% and a 10% inflation factor to anticipate study deviations (missing data, withdrawal, loss to follow-up).

Participants are recruited in the hospital when they come for a medical consultation or at the end of a hospitalisation for complications. Potential participants are screened. The investigator informs the patient and caregiver about the study, following which the patient gives oral consent and the patient’s caregiver the written informed consent for patient participation. The information note and consent form is presented in Additional file 1. When the patient legally becomes an adult (i.e. at 18 years of age in France), he will give his/her own written informed consent.

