#### Arm A – control group

Patients and caregivers randomised to the control group receive the standard care management used in the study centre, including a joint consultation with a paediatrician and an internist/haematologist between the age of 16 and 18 years, and a visit to the adult department of care.

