#### Arm B – intervention group

In addition to standard management, patients and caregivers randomised to the intervention group benefit from the SCD paediatric-adult transition programme. Based on the biopsychosocial approach, this consists of three structured axes, the objectives of which and practical details are summarised in Table 1.

**Table 1 Tab1:** The three axes of paediatric-adult transition programme

Axes	Public	Objectives	Contents	Practical details	Providers
Educative	Patient and caregiver dyad	Providing self-care knowledge and skills related to SCD and therapeutics	Knowledge and coping skills, with patient needs assessment	Face to face At patients’ home 3 sessions of 2 h	One healthcare professional, trained in patient education and in SCD
Psychological	Individual patient i	Helping empower patients in relation to pain management and emotions	Knowledge and coping skills, with patient needs assessment	Face to face At hospital 6 sessions of 1.5 h	One healthcare professional, trained in therapeutic hypnosis and in SCD
Social	Group of 4 to 8 patients	Facilitating the relationship with oneself, others, and care	Coping skills	Face toface At ‘neutral place’ as association patient place 2 sessions of 2 h	One healthcare professional and one expert patient, both trained in patient education and in SCD

*h* hour*, SCD* sickle cell disease

The modifiable factors are used as coping skills during the educative, the psychological, and the social axis. The objective of the educative axis is to provide knowledge and coping skills related to self-care management. It is conducted at home with the patient and his/her parent by a healthcare professional trained in patient education. The objective of the psychological axis is to help empower patients in relation to pain management and emotions. It is conducted at hospital with only the patient by a healthcare professional trained in therapeutic hypnosis. The objective of the social axis is to facilitate the relationship to oneself, others, and care. It is conducted in a ‘neutral place’ (not at home and not at the hospital) with a group of patients by a healthcare professional trained in patient education and an expert adult patient also trained in patient education.

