### Statistical analysis plan

Demographics and other characteristics are reported descriptively and according to treatment group. Means and standard deviation (SD), or medians and ranges when appropriate are calculated for continuous variables. Categorical variables will be presented using numbers and percentages.

The crude rate of hospitalisations due to complications will be calculated by dividing the total number of hospitalisations due to VOC, ACS, and stroke occurring after transfer by the total duration of follow-up of all patients in each group. The treatment effect will be assessed using a multivariable Poisson regression model with the study group as a factor, adjusting for minimisation factors and relevant patient characteristics and the length of follow-up as the offset. Results will be expressed as a rate ratio with 95% confidence interval. A negative binomial model will be fitted if data are over-dispersed. The same analyses will be performed for the association between intervention and other secondary outcomes.

Analysis of covariance (ANCOVA) will be used to evaluate the intervention effect at T-24 on all the secondary outcomes evaluated by questionnaires. Scores will be computed and depicted at each assessment by following the scoring procedures for each questionnaire. Each ANCOVA will include the baseline measure (T-inclusion) and minimisation factors as covariates. Changes over time for each score will be also assessed using generalized estimation equation analyses to test the effect of group, time, and the interaction group time after controlling for minimisation factors and relevant patient characteristics.

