The major strength of the DREPADO trial is the proposed intervention using a biopsychosocial, whole system approach to the patient, which aims to reflect as much as possible the real needs of patients and their family. In addition, needs are assessed at the beginning of the psychological and educative axes, in order to individualise the intervention. Another strength of the intervention is the participation of expert patients in the social axis; his/her experiential knowledge promotes sharing between the adolescents in the group and provides real-life examples of coping skills and advice [22]. The major limitation of DREPADO trial is the difficulty to implement the transition programme, as the intervention is complex [23]; it involves different departments of care, different places of intervention (home, hospital, ‘neutral place’), and different types of expertise (or the training of personnel in several different fields). This complexity requires good communication and coordination between interlocutors; to aid in this regard, the DREPADO study group provides each centre tools for communication and training. Another potential limitation is patient adherence to the programme, and the strategies to improve this are also based on communication, using, for example, paper schedules and reminder text messages.

The DREPADO RCT has multiple perspectives. First of all, for patients and their parents, this trial should show a better health status, quality of life, and a better experience of this difficult period of care. For healthcare professionals, it is expected to provide a model of paediatric-adult care transition for SCD. Furthermore, the methodological quality renders possible the evaluation of the efficacy and efficiency of the proposed programme. If conclusive, it will be possible to adapt it and test it in other chronic diseases presenting the same care transition problem [2]. For public health, the DREPADO trial results will be multiple. By focusing on this population of sub-Saharan origin with low visibility and high social vulnerability [24], this study will reduce the social inequalities in the healthcare system experienced by patients with SCD and their families. Also, by improving the health status, quality of life, and care of patients with SCD, the indirect cost of complications will decrease.

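### One dropout rule covers missed programme sessions and missed evaluations, giving Arm B up to 11 extra triggers; if dropout status ends follow-up, this can cause unequal loss from a records-based primary outcome.

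*Protocol article*

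**What the plan says.** The rule under Withdrawal and discontinuation is: "Participants who are not present at intervention and/or evaluation are contacted by telephone; after four unsuccessful calls, participants are considered dropouts". It treats absence from the programme and absence from an evaluation alike.

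Only one arm has a programme to miss. For Arm A: "Patients and caregivers randomised to the control group receive the standard care management used in the study centre". For Arm B: "In addition to standard management, patients and caregivers randomised to the intervention group benefit from the SCD paediatric-adult transition programme". Table 1 lists an educative axis ("3 sessions of 2 h"), a psychological axis ("6 sessions of 1.5 h") and a social axis of two sessions. The Discussion says that the programme starts in the paediatric department and continues in the adult one.

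The primary outcome (Outcome measurements) counts admissions and emergencies for complications at the index hospital in the two years after the first adult consultation. Table 2 gives medical records as the source. The Statistical analysis plan section uses length of follow-up as the offset. Sample size and recruitment adds "a 10% inflation factor to anticipate study deviations (missing data, withdrawal, loss to follow-up"), one figure for both arms. The trial is open-label.

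**The concern.** A patient can stop attending the programme and still be followed through hospital records. The rule does not make that distinction. A hard-to-reach adolescent in Arm B meets it at any of 11 sessions as well as at the evaluations. A similar adolescent in Arm A meets it only at the evaluations. If dropout status ends follow-up, the patients left in the two arms may no longer be comparable, and the primary rate ratio would partly reflect who was kept. An Arm B patient dropped before transfer would contribute no follow-up time at all. The Discussion recognises that the trigger could come into play: "Another potential limitation is patient adherence to the programme". Bias of this kind is not reduced by a larger sample, and follow-up that was never collected may be hard to recover later.

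**Working it through.** **1. Count the triggers.** Evaluations after inclusion, both arms: T-transfer, T-12, T-24, so 3. Programme sessions, Arm B only: 3 + 6 + 2 = 11. The rule can therefore be set off at up to 3 occasions in Arm A and up to 3 + 11 = 14 in Arm B. In each case four failed calls must follow.

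**2. Reproduce the sample size, to see how lost patients are treated.** Inputs from Sample size and recruitment: control rate 3.5 per patient-year, 2 years, rate ratio 0.85, 80% power, two-sided 5%, 10% inflation. The article names no formula. The Signorini formula for Poisson regression gives

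N = [1.960 × √4 + 0.842 × √(2 + 2/0.85)]² / (3.5 × 2 × (ln 0.85)²) = 174.2, so 88 per arm.

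88 / 0.90 = 97.8, so 98 per arm and 196 in total, which matches the stated figure. A Wald or log-rate form gives 93 per arm, or 104 after inflation, which does not match. In the matching calculation, the 10% who are lost add nothing to the hospitalisation-rate comparison, and the loss is assumed equal in the two arms.

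**3. Size of a possible bias.** Assume no true effect, the same average rate in both arms, and a share p of Arm B removed with no follow-up time counted. Those removed have h times the average rate. The rate among those who stay in Arm B is then (1 − ph)/(1 − p) times the average, and this is the observed rate ratio. The documents give neither p nor h; both are assumptions.

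| h | p = 10% | p = 20% |
|---|---|---|
| 0.5 | 0.95/0.90 = 1.06 | 0.90/0.80 = 1.13 |
| 1 | 1.00 | 1.00 |
| 1.5 | 0.85/0.90 = 0.94 | 0.70/0.80 = 0.875 |
| 2 | 0.80/0.90 = 0.89 | 0.60/0.80 = 0.75 |

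On the log scale, 0.94 is ln(0.944)/ln(0.85) = 35% of the target effect.

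**4. Cross-check with loss in both arms.** Let both arms lose 10% and Arm B a further share e, whose rate is r times that of the patients who stay. The observed rate ratio is 0.90/[(0.90 − e) + e × r]. For e = 10% it is 1.06, 1.00 and 0.90 at r = 0.5, 1 and 2. For e = 20% it is 1.13, 1.00 and 0.82.

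**5. Power.** With the log-rate Poisson form and 88 patients kept in Arm A, power is 78.1% if Arm B keeps 88 and 75.3% if it keeps 78. The loss of power is modest; the issue is bias.

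**The case against.** The strongest reply is that the article only labels such patients dropouts. It does not say that record abstraction stops, that data are discarded or that anyone leaves the analysis. The offset can accommodate unequal follow-up, and the handling of data after dropout may well be set out in the full protocol or analysis plan, which are not shown. This stands. A reader might infer that the rule removes disengaged Arm B patients from the primary comparison, but the text does not establish that. The 10% allowance points that way without proving it.

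Four further points stand:

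- A missed session alone is not enough. A patient who skips sessions but answers the telephone is not a dropout.
- The evaluation trigger applies to both arms, so an unreachable Arm A patient can also become a dropout, at fewer contact points.
- The programme continues after transfer. A patient lost late could still contribute time and events, which would make the bias smaller than in the table.
- Records alone do not settle everything. A patient who never attends the first adult consultation has no start date for the outcome window, and questionnaires do need contact.

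The Discussion also calls adherence only a potential limitation and lists paper schedules and text reminders as countermeasures.

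A reader might extend the point to the T-24 ANCOVA, which depends on patients returning. The article already plans generalised estimating equations over time for the same scores, so the dropout wording gives no ground for replacing those analyses.

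What the reply does not remove is the asymmetry: the rule as worded has a trigger that exists in one arm only, and the primary outcome does not need it.

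**Conclusion.** The point holds as a risk that the wording creates, and it should be fixed. The rule gives Arm B up to 11 extra triggers for dropout status. If that status ends follow-up, it can produce differential attrition in an open-label trial. Whether it does so depends on a step that the article leaves open.

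The size and sign of any bias are unknown. With 10% of Arm B lost in this way and no true effect, the rate ratio is 0.94 or 0.89 if those patients have 1.5 or 2 times the average rate, 1.00 at equal risk, and 1.06 at half the rate, against a target of 0.85. A reader might infer that the bias must favour the programme, because the article links discontinuity of care with morbidity. It gives no event rates for non-attenders, however. Patients with mild disease may skip sessions, and disengaged patients may avoid the index hospital, where events are counted. The planned 196 is not affected.

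**What to change.** In Withdrawal and discontinuation:

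- Define stopping the programme separately from leaving the study.
- State that missed sessions, even when followed by failed calls, do not end study follow-up, and that the four-call rule stops only questionnaire collection that depends on contact.
- State that admissions and emergencies continue to be abstracted from records to T-24 for all randomised patients who reach transfer, and are analysed in the assigned arm. This applies as far as consent permits, including the patient's own written consent at 18 described under Sample size and recruitment, and unless consent is withdrawn.
- Report by arm the dropouts by trigger (session or evaluation) and the patients who never transfer.

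The cost is a wording change and minor extra record abstraction. The sample size and the planned ANCOVA and estimating-equation analyses need no change on this account.

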### Sample size and recruitment

A total of 196 (98 in each group) is required to detect at least a 15% reduction of the hospitalisation rate for complications 2 years after the transfer in the intervention group compared to the control group. This reduction assumes a hospitalisation rate of 3.5 per patient per year [7] with 80% power and the use of a two-sided test at a significance level of 5% and a 10% inflation factor to anticipate study deviations (missing data, withdrawal, loss to follow-up).

Participants are recruited in the hospital when they come for a medical consultation or at the end of a hospitalisation for complications. Potential participants are screened. The investigator informs the patient and caregiver about the study, following which the patient gives oral consent and the patient’s caregiver the written informed consent for patient participation. The information note and consent form is presented in Additional file 1. When the patient legally becomes an adult (i.e. at 18 years of age in France), he will give his/her own written informed consent.

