### Randomisation and blinding

Participants are randomly assigned to one of the two groups at a 1:1 ratio using a minimisation algorithm. The minimisation factors are the centre, the type of SCD, and the occurrence of VOC during the year before inclusion. Allocation is done using a central randomisation system (Ennov Clinical, version 7.5.710.4, San Francisco, CA, USA). At each centre, a clinical research associate delegated by the investigator and who is trained in good clinical practice (GCP) logs into the central randomisation system and inputs patient information; a random number and group assignment are then immediately given by the system. Because DREPADO is an open-label trial, the clinical research associate directly informs the patient-caregiver dyad of the arm to which they are assigned (Arm A or B).

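### The 196-patient, 80%-power statement reproduces only with a pure Poisson variance, so the power is conditional on almost no residual between-patient variation, and the protocol does not say so

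*Protocol article*

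**What the plan says.** In the protocol article, Sample size and recruitment fixes the size and target: "A total of 196 (98 in each group) is required to detect at least a 15% reduction of the hospitalisation rate for complications". The remaining inputs follow: "This reduction assumes a hospitalisation rate of 3.5 per patient per year [7] with 80% power and the use of a two-sided test", a 5% level, and 10% inflation that the text assigns to missing data, withdrawal and loss to follow-up. No standard deviation, dispersion parameter or between-patient variance appears.

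The section Statistical analysis plan names a Poisson regression with length of follow-up as offset, adjusted for the minimisation factors and relevant patient characteristics. It then adds: "A negative binomial model will be fitted if data are over-dispersed".

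The inclusion criteria admit three forms of the disease (SS, SC and Sβ). Randomisation and blinding states: "The minimisation factors are the centre, the type of SCD, and the occurrence of VOC during the year before inclusion".

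**The concern.** A Poisson calculation treats all patients in an arm as sharing one event rate. Repeated hospitalisations in a mixed population may well vary more than that, and the analysis section makes provision for it. If they do, the standard error of the log rate ratio exceeds the one used to size the trial, and the 80% no longer applies.

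This concerns the primary comparison. A non-significant result read against a claimed 80% power would suggest that a 15% reduction had been reasonably ruled out, when the trial may have had much less chance of detecting it. A useful programme could be dismissed on that reading.

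**Working it through.** **Inputs from the article.** Control rate 3.5 per patient-year; rate ratio 0.85; two years after transfer; 1:1 allocation; two-sided 5% (z = 1.960); 80% power (z = 0.842); 10% inflation. Expected events per patient are 3.5 × 2 = 7.0 in Arm A and 7.0 × 0.85 = 5.95 in Arm B. ln(0.85) = −0.1625.

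**Step 1: reproduce the stated size.** The Signorini formula for Poisson regression, with a binary covariate, dispersion 1 and null variance at the control rate, gives per arm

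n = [1.960 × √4 + 0.842 × √(2 + 2/0.85)]² / (2 × 7.0 × 0.1625²) = 32.22 / 0.3698 = 87.1, rounded up to 88.

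88 / 0.9 = 97.8, rounded up to 98 per arm, 196 in total. This matches exactly.

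Other two-sided Poisson variants come close but a little higher. For example, the Wald test on the log rate ratio gives (1.960 + 0.842)² × (1/7 + 1/5.95) / 0.1625² = 92.4, so 93 per arm. Across the rate-difference, Wald, square-root and pooled-null forms, the inflated total is 204 to 208. One-year exposure (376 to 412) and a one-sided 5% test (162 to 164) do not match.

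**Step 2: how much over-dispersion could 196 absorb?** With negative binomial counts, variance = μ + kμ², and

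Var(log RR) = (1/7 + 1/5.95 + 2k) / n = (0.311 + 2k) / n.

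Even if all 98 per arm were evaluable, 80% power on the Wald test requires

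k ≤ [98 × 0.1625² / (1.960 + 0.842)² − 0.311] / 2 ≈ 0.009.

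**Step 3: power over a range of k.** The documents give no k, so these values are assumptions. Power = Φ(0.1625/SE − 1.960), with SE from the formula above.

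| Residual k | 0.311 + 2k | Power, 88 per arm | Power, 98 per arm | Rate ratio detectable with 80% power, 88 per arm |
|---|---|---|---|---|
| 0 | 0.311 | 78% | 82% | 0.85 |
| 0.05 | 0.411 | 66% | 71% | 0.82 |
| 0.1 | 0.511 | 57% | 61% | 0.81 |
| 0.2 | 0.711 | 44% | 48% | 0.78 |
| 0.5 | 1.311 | 27% | 29% | 0.71 |
| 1.0 | 2.311 | 17% | 18% | 0.63 |

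The detectable ratio solves the power equation with the Arm B mean set to 7 × RR. Holding the variance at its value for 0.85 instead moves the entries for k = 0.05 and k = 1.0 to 0.83 and 0.64. The 78% at k = 0 is the Wald figure; the Signorini form gives 80% at the same size.

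For scale, k = 0.05 means patient rates with a standard deviation of √0.05 = 22% of the mean.

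**Step 4: simulation.** With 88 per arm and 600 runs, power was 78% for Poisson data. With a negative binomial fit it was 42% at k = 0.2, 28% at k = 0.5 and 16% at k = 1.0, in line with the table.

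**The case against.** The calculation contains no slip: the stated inputs yield the stated size. The issue is an unstated variance assumption. It might also be said that a journal article need not print every assumption. That would answer a complaint about a missing detail, but here the printed number itself shows that dispersion was set to 1, and the 10% is reserved for other purposes.

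The strongest objection is that the primary model adjusts for centre, disease type, prior crises and other characteristics. Variation explained by these leaves the residual k, which is the k that matters for power. This stands, and it is why the range should start low. It does not rescue the 80%, because residual k would have to fall to about 0.01 or less.

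It is also fair that the switch to a negative binomial model is a conditional safeguard. It does not admit that over-dispersion is expected. It protects the type I error, and the planned confidence interval will show the precision achieved. Neither restores power.

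Two further arguments are tempting but unsupported:

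- **Prior-year crises.** A Poisson rate of 3.5 per year leaves few event-free years, so a reader might infer that minimising on crises in the previous year proves heterogeneity. But 3.5 is a hospitalisation rate assumed for the period after transfer, and the factor concerns crises before inclusion. The two are not comparable.
- **Recruitment setting.** Patients are approached "when they come for a medical consultation or at the end of a hospitalisation for complications". A reader might infer a mixture of stable and unstable patients. The article describes only occasions of contact, the same patient could be met at either, and counting starts at transfer.

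**Conclusion.** The point holds as a conditional one. The 80% power for a 15% reduction applies only if residual over-dispersion is negligible, and the article does not state that condition, although its analysis section provides for the case in which it fails.

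The existence of the dependence is firm: 196 reproduces with dispersion 1, and a k of about 0.009 exhausts the margin even without dropout. The size of the loss is not firm. It rests on an assumed residual k, on negative binomial variation, on full two-year exposure for 88 patients per arm, and on the stated control rate. Over k from 0.05 to 1.0, power runs from about 66% down to 17%.

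A reader might go further and infer that the trial is bound to be severely underpowered, or that the negative binomial model will almost certainly be used. The documents give no k and make the switch conditional, so neither follows. No single corrected sample size follows either.

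**What to change.** Keep 196 patients and change the wording:

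1. In Sample size and recruitment, state that 80% power for a 15% reduction assumes Poisson variation with negligible residual over-dispersion.
2. Add power, or the rate ratio detectable with 80% power, for residual k from about 0.05 to 1.0, as in the table above, marked as assumed values.
3. In Statistical analysis plan, name the negative binomial model, or Poisson regression with robust variance, as the primary model in advance, replacing the data-driven switch.
4. State that a non-significant primary result will be interpreted through the confidence interval for the rate ratio, without appeal to the nominal 80%.

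The cost is protocol and analysis-plan text only; recruitment and patient care are unaffected. The stated power becomes less favourable, and these changes do not raise the power itself.
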